### Intervention conditions

#### *KMC condition*

If the infant is randomized to the KMC condition, the research nurse will begin by recording a one-minute sample of the infant in the incubator. The research nurse will then place the mother and infant into the KMC condition, where the diaper-clad infant is help upright, at an angle of approximately 60°, between the mothers breasts, providing maximal skin-to-skin contact between mother and baby. The infant will remain in KMC for at least 15 minutes prior to the painful procedure. Two minutes prior to the procedure the infant will receive ¼ of the recommended (based on NICU protocol) volume of sterile water by syringe onto the tongue. The remainder of the total recommended dose will be given as needed in small increments during the procedure.

#### *Sucrose condition*

If the assigned condition is sucrose alone, half an hour before the procedure the nurse will place the infant in the supine position in an incubator or infant cot and set up the monitoring equipment. All monitoring will take place while the infant is in the incubator or cot. Two minutes prior to the procedure, the baby will receive ¼ of the recommended volume (based on NICU protocol) of 24% oral sucrose solution by syringe onto the tongue. The remainder of the total recommended dose may be given as needed in small increments during the procedure.

#### *Combined KMC and sucrose condition*

For combined sucrose and KMC, the infant will be placed in KMC as described for the KMC alone condition, however, will receive 24% oral sucrose solution as per the NICU protocol described above.

Although most painful procedures will not be video-recorded for the study analysis, the expectation is that the staff caring for infants enrolled in the study will follow the study intervention protocol for all painful procedures, and that any deviations from the study protocol will be charted and included in the analyses. Babies in the KMC group will have reminder signs at the bedside prompting the staff to place them in KMC for procedures, and the study syringes of either 24% sucrose solution or sterile water will be available to staff at the bedside throughout the infant’s stay in the NICU. Staff documentation of all painful procedures will be monitored to ensure compliance with the study protocol.

In order to ensure equipoise, staff may deviate from the protocol to give off-study doses of rescue sucrose if the infant has a PIPP score > 6 (considered to indicate pain) at their discretion. The deviations from protocol will be recorded on a procedure record kept at each infant’s bedside. If the mother is unavailable for a painful procedure, the infant will be swaddled and given the study solution. If the infant has a PIPP score > 6, off-study sucrose may be given by the nurse caring for the patient. All off-study sucrose doses will be recorded in the procedure record and the research nurse will confirm the doses given from the medication administration record.

### Outcomes

#### *Premature Infant Pain Profile (PIPP)*

The primary outcome in this trial will be infant pain intensity measured by the Premature Infant Pain Profile (PIPP) [72,88]. The PIPP uses seven indicators to calculate a composite pain measure: three behavioral indicators (facial actions of brow bulge, eye squeeze, and nasolabial furrow), 2 physiological indicators (heart rate and oxygen saturation), and 2 contextual indicators (gestational age and behavioral state) [72]. The contextual factors included in the PIPP are particularly important for this study as infants are being followed over time and therefore age changes will be accounted for. In addition, KMC is known to promote quiet sleep state, and this will be accounted for when considering behavioral state as an indicator in the PIPP scoring. The PIPP was developed 13 years ago and has steadily accumulated evidence of reliability and validity [72,88]. It had been used in over 40 studies to date [88].

This study will utilize a Somte (Compumedics, Melbourne, Australia) system that samples at a rate of 256 Hz to measure physiological data. Heart rate and oxygen saturation are recorded to the Somte system using a transcutaneous probe, and Electrocardiogram (ECG) is recorded from 3 leads. Epochs will be noted with an event timer in the Somte system. Close up video recordings of the infants face will be made using a Sony DCR-SR82 HDD digital video camera in the first baseline in the incubator (Baseline 1), one minute prior to start of procedure (Baseline 2), and during and after the procedure. The neurobehavioral state component of the PIPP score is determined according to Prechtl’s categories of quiet sleep, quiet awake, active sleep, or active awake [89], during the baseline [90]. Gestational age will be taken from the infant chart, and will be based on ultrasound at 16 weeks.

All data will be analyzed in the research laboratory outside the NICU. Physiologic data will be analyzed using Compumedics E-series Profusion PSG II software. Faces will be coded second-to-second on a stop frame system by trained coders naïve to the purpose of the study. Coders will be trained up to 90% agreement on video recordings from previous studies. Every three months, coders will recode randomly selected sessions (one from their earlier coding and one from each of the other coders) in order to determine both inter and intra-rater reliability.

#### *Neurobehavioral Assessment of the Preterm Infant (NAPI)*

The secondary outcome will be the Neurobehavioral Assessment of the Preterm Infant (NAPI), developed by Korner and colleagues [91-95]. In particular, the subscales of alertness and orientation and motor development and vigor will be assessed. The NAPI evaluates the relative maturity of functioning of preterm infants, with higher scores reflecting higher maturity, and can differentiate 2 weeks’ post-conceptual age. Assessments at 32 and 36 weeks corrected gestational age and at term equivalence will be preformed on all infants in accordance with their gestational age at birth, as well as at the time of discharge from the NICU. Much of the NAPI examination consists of observational items, and the remainder rates the infant’s response to stimuli. The assessment takes approximately 30 minutes to administer and includes clusters of single-item neurobehavioral dimensions. Test – re-test reliability ranging over 2 consecutive days ranged from 0.59 to 0.90. Original inter-observer reliability ranged from 0.64 to 0.93 [91]. Clinical and construct validity and sensitivity of the NAPI have been established [94,96].

### Other outcomes

Severity of medical risk at birth will be assessed by the SNAP-II (Simplified Newborn Illness Severity and Mortality Risk Score). Daily number tissue-damaging procedures will be recorded from the chart and the number of hours spent in KMC will be taken from a diary given to the mother. Mothers will also provide baseline salivary cortisol samples upon awakening on the days infants undergo a video-recorded medically required painful procedure.

### Statistical analysis

Analysis and inference will be based on the intention-to-treat principle. Descriptive and correlational analysis will be performed to identify potential confounding variables. The data will be analyzed using growth curve analysis. In this analysis, a regression line is fitted to each infant’s responses over time, and a slope and intercept is derived for each curve. The data will be centered so that the last time period is coded as 0, allowing for the comparison of the three groups, as well as the differences at final assessment. The advantage of this analysis is that 1) data can be missing as long as there are three data points, and 2) the spacing of the interventions does not have to be the same for all participants. This analysis will therefore answer all research questions: 1) what is the trend across time? (i.e., comparing slopes), 2) is KMC more efficacious than sucrose at reducing pain? (i.e., comparing the intercepts at the final assessment), and 3) is the combination of KMC and sucrose more powerful than either alone? Potential cofounders that may need accounting for in the statistical model include number of tissue damaging procedures, number of hours of KMC in total, number of doses of sucrose in total, SNAP-II score at birth, and gestational age at birth in days.

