**Methods/design:**

Infants admitted to the NICU who are less than 36 6/7 weeks gestational age (according to early ultrasound), that are stable enough to be held in KMC, will be considered eligible (N = 258). Using a single-blinded randomized parallel group design, participants will be assigned to one of three possible interventions: 1) KMC, 2) combined KMC and sucrose, and 3) sucrose alone, when they undergo any routine painful procedure (heel lance, venipuncture, intravenous, oro/nasogastric insertion). The primary outcome is infant’s pain intensity, which will be assessed using the Premature Infant Pain Profile (PIPP). The secondary outcome will be maturity of neurobehavioral functioning, as measured by the Neurobehavioral Assessment of the Preterm Infant (NAPI). Gestational age, cumulative exposure to KMC provided during non-pain contexts, and maternal cortisol levels will be considered in the analysis. Clinical feasibility will be accounted for from nurse and maternal questionnaires.

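### Total sucrose doses and total KMC hours are listed as possible adjustment variables, although both follow randomisation and are largely the assigned treatment

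*Protocol article*

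**What the plan says.** The Statistical analysis section opens with "Analysis and inference will be based on the intention-to-treat principle". It continues: "Descriptive and correlational analysis will be performed to identify potential confounding variables". After describing the growth-curve model it gives the candidates, introduced by "Potential cofounders that may need accounting for in the statistical model include". The list is "number of tissue damaging procedures, number of hours of KMC in total, number of doses of sucrose in total", followed by SNAP-II and gestational age, both at birth.

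Other sections bear on what these totals contain:

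- **Sucrose.** Under KMC condition, infants in KMC alone get sterile water. Under Sucrose condition and Combined KMC and sucrose condition, the other two arms get 24% sucrose. Staff are expected to follow the assigned arm at every painful procedure, recorded or not.
- **Off-study sucrose.** Combined KMC and sucrose condition and Ethical considerations both allow it, at staff discretion, when PIPP exceeds 6.
- **KMC hours.** KMC condition requires at least 15 minutes in KMC before each procedure. The abstract describes a narrower variable than the analysis section: "cumulative exposure to KMC provided during non-pain contexts, and maternal cortisol levels will be considered in the analysis".
- **Procedures.** Other outcomes says "Daily number tissue-damaging procedures will be recorded from the chart".
- **Deviations.** Combined KMC and sucrose condition says that "any deviations from the study protocol will be charted and included in the analyses".

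**The concern.** A variable that arises after randomisation cannot confound a randomised comparison. If it is part of the treatment, or responds to the outcome, conditioning on it changes the question. Comparing KMC alone with sucrose alone at equal total sucrose doses no longer estimates the effect of assignment, which is what the intention-to-treat statement promises. Whole-stay totals also count exposure that came after the earlier PIPP recordings.

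Selection by correlation adds to the risk. Variables driven by arm or by PIPP are the ones likely to correlate with PIPP and so to be chosen. The choice would then be made from the data, between models that can give different answers to the trial's main question.

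**Working it through.** **1. The planned comparison.** Inputs from Sample size: difference 1.5, SD 3, power 0.9, N = 258. Two-sided 5% and equal allocation are assumed, since neither is stated.

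- n per arm = 2(1.960 + 1.282)² × 3² / 1.5² = 84.1, so 85. Three arms give 255, close to 258 = 3 × 86.
- SE = 3 × √(2/86) = 0.457. Power = Φ(1.5/0.457 − 1.96) = Φ(1.32) = 0.906.

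The planned figure reproduces, and any loss below is measured from SE 0.46 and power about 0.90.

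**2. The five candidates.**

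| Variable | Fixed at randomisation? | Link to arm or outcome |
|---|---|---|
| SNAP-II at birth | yes | none |
| Gestational age at birth | yes | none |
| Total sucrose doses | no | set by arm, and raised by rescue when PIPP > 6 |
| Total KMC hours | no | includes procedural KMC in two arms |
| Number of procedures | no | routine care; no effect of arm is stated |

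The remaining steps are least-squares simulations of one PIPP score per infant, with a true KMC-minus-sucrose effect of -1.5. Procedure counts, rescue rates and KMC hours are assumptions, because the article gives none.

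**3. Precision.** Assume a mean of 30 procedures (log-SD 0.4-0.6), rescue at 15% of KMC-alone procedures whatever the PIPP, and procedure count unrelated to PIPP.

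- Doses only: SE 0.54-0.63. By formula, Φ(1.5/0.54 − 1.96) = 0.79 and Φ(1.5/0.63 − 1.96) = 0.66; simulated power was 0.78 and 0.68.
- All three totals: SE 0.73-1.00, power about 0.34-0.56 (the range also covers runs where severity matters, as in step 4).

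**4. Bias through illness severity.** Now let sicker infants have more procedures and a higher PIPP (1 point per SD).

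- Doses without procedure count: the mean estimate moves to between about -0.3 and +0.3.
- Doses plus procedure count: -1.57 to -1.48.
- All three totals: about -1.5.

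Under this mechanism the full list costs precision but causes no material bias.

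**5. Bias through rescue tied to PIPP > 6.** Assume about 33 procedures per infant, 0.5 h of KMC per procedure, the mother available for 80% of them, and other KMC of mean 20 h (SD 10).

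| Share of procedures with PIPP > 6 given off-study sucrose | Doses only: estimate (SE), power | All three totals: estimate (SE) |
|---|---|---|
| 0% | -1.49 (0.66), 0.61 | -1.53 (0.96) |
| 10% | -1.19 (0.65), 0.43 | -0.54 (0.95) |
| 25% | -0.84 (0.63), 0.27 | +0.65 (0.92) |
| 50% | -0.50 (0.60), 0.13 | +1.80 (0.83) |
| 90% | -0.20 (0.56), 0.05 | +2.39 (0.71) |

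The mechanism is simple. In the doses-only model, adjusted effect = unadjusted effect − slope × difference in mean doses. At 25%, KMC alone averages 3.6 doses and sucrose alone 33 + 5.2 = 38.2, a difference of -34.6. Going from -1.48 to -0.84 then needs a slope of only 0.64/34.6 = 0.018 PIPP points per dose. Here adding procedure count does not help: at a given count, extra doses mark infants with higher PIPP.

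**6. KMC hours.** If the benefit runs through procedural KMC hours, adjusting for total hours gives -0.21, -0.77, -1.23 and -1.38 as the SD of other KMC hours goes from 2 to 5, 10 and 20 h. If it does not, the estimate is unbiased, with SE 0.51 and power about 0.83-0.85.

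**7. Procedure count alone.** With no effect of arm on the count, the estimate stays at about -1.5 and power at about 0.90.

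**The case against.** The strongest reply is that nothing is fixed. The text gives candidates that may need accounting for, and the final covariate set belongs in an analysis plan that is not shown. This stands as far as it goes: a reader might infer that the primary model will adjust for these totals, and the article does not say so. But naming them as candidates, with correlation as the selection rule, is a stated choice and not a missing detail.

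Other stronger readings also fail:

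- *All three totals are equally harmful.* Procedure count is routine care, and step 7 shows no harm unless arm affects it. Its place under Other outcomes proves nothing, since SNAP-II at birth sits under the same heading.
- *Adjustment takes the effect to about zero whatever the model.* The range of -0.3 to +0.3 belongs to a model with doses but without procedure count. With the count added, that mechanism gives about -1.5. Bias in the full list needs rescue to follow PIPP.
- *Every contrast is collinear with arm.* Sucrose alone and the combination both receive sucrose. With rescue unrelated to PIPP, their contrast stayed near -2.0 after dose adjustment. The damage falls mainly on contrasts with KMC alone.
- *The KMC-hours variable certainly contains treatment.* In the analysis section the total may simply mean cumulative over the stay, and the abstract limits the variable to KMC outside painful procedures. The two sections conflict, and the article does not settle which is meant.
- *Deviations and maternal cortisol will be covariates.* The article says that deviations are included in the analyses, not how. Procedures already labels the cortisol data exploratory.
- *Intention-to-treat is flatly contradicted.* Infants can still be analysed as assigned. What is lost is that the arm coefficient estimates the effect of assignment.

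**Conclusion.** The concern holds for total sucrose doses, and for KMC hours if these include procedural KMC. Doses are the worse of the two, being set by arm and also open to the outcome scale through rescue. The loss of precision on the KMC-alone contrast appeared in every dose-adjusted run. Bias towards or past zero depends on how closely off-study sucrose tracks PIPP above 6, which the documents do not let one estimate.

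The sizes rest on assumed procedure counts, rescue rates and KMC hours, and on a single-time regression in place of the planned growth curve with at least three sessions. They illustrate the risk and do not forecast the trial's result.

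**What to change.** Replace the sentence on possible confounders with a rule of this kind: the primary growth-curve model contains arm, time, arm-by-time and only variables fixed at randomisation, namely gestational age at birth and SNAP-II. Sucrose doses, KMC hours, procedure counts and charted deviations are reported by arm and used only in analyses labelled exploratory. Drop correlation screening as the route into the primary model.

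Reconcile the definition of KMC exposure between the abstract (outside painful procedures) and the Statistical analysis section (in total). Even the narrower version follows randomisation, so it belongs in the exploratory set.

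The cost is a few lines of text, settled before the data are unblinded. No new data and no more infants are needed, and the planned power of about 0.90 for the 1.5-point difference is kept.

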### Ethical considerations

Authorization and informed consent will be obtained from the mother of each eligible infant prior to study entry, and a copy of the consent form will be provided to participants once signed. Participation in the study is voluntary, and mothers will be made aware of their rights to withdraw their infants’ participation at any time throughout the course of the study. This study provides no direct benefit for the mothers or infants enrolled and compensation for study participation will not be offered.

Provision of KMC during painful procedures is not considered to be a standard of care in the NICU at the study site. While KMC is considered a safe practice for stable infants, all participants will be closely monitored with regard to any adverse events associated with being transferred into KMC. Administration of sucrose is considered standard care in the NICU at the study site. In order to ensure equipoise, NICU staff will be permitted to give off-study doses of sucrose if the infant has a PIPP score greater than 6, which is indicative of pain. Infants will be monitored as per NICU standard of care, and their clinical condition will be evaluated daily as part of medical rounds. All procedures that infants undergo will be part of their routine NICU care and will not be conducted solely for the purpose of this study.

## Discussion

This will be the first study to examine the repeated use of KMC for reducing pain response in preterm neonates. It is also the first to compare sucrose to KMC, or the interventions in combination, across time. Based on the theoretical framework of the brain opioid theory of attachment, it is fully expected that the results will be as hypothesized. However, current pain management guidelines are based on minimal data on repeated use of either intervention. Therefore, regardless of the outcomes of this study, results will have important implications for guidelines and practices related to management of procedural pain in preterm infants.

## Abbreviations

SSC: Skin-to-skin contact; KMC: Kangaroo Mother Care; NICU: Neonatal Intensive Care Unit; PIPP: Premature Infant Pain Profile; NAPI: Neurodevelopmental Assessment of the Preterm Infant; SNAP-II: Simplified Newborn Illness Severity and Mortality Risk Score.
